**Design:**

This article describes the rationale and protocol of a prospective, open, interventive, balanced, bi-centric, pilot randomized controlled trial (RCT). A total of 32 patients with a primary SCID diagnosis of social anxiety disorder will be randomized to either CBT or ST. Both treatments will be manualized.

The primary outcome will include social anxiety symptoms at the end of therapy. Therapy will be restricted to no more than 26 hours (primary endpoint). Secondary outcomes will include psychological, social systems and interpersonal functioning, symptom adjustment, and caregiver burden, in addition to change measures, therapist variables and treatment adherence. At the secondary endpoints, 9 and 12 months after the beginning of therapy, we will again assess all outcomes.

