## Hypotheses

The main focus of this paper is to answer the question of what effect sizes of ST can be expected compared to CBT, to calculate how many patients will be needed to replicate effects indicated in this study. For that purpose, we descriptively and exploratively analyze the following hypotheses.**H1: Effects for social anxiety at the end of therapy (primary endpoint).** According to the SOPHO-NET [36] and the study by Willutzki and colleagues [5], we expect both CBT and ST to demonstrate a reduction of social anxiety symptoms, and that CBT will show a major change compared to the new ST.**H2: Effects for secondary outcomes at the end of therapy (primary endpoint).** According to the SOPHO-NET [36], we expect CBT to demonstrate a major change compared to the new ST on psychological functioning, social system and interpersonal functioning, symptom adjustment, and caregiver burden.**H3: Effects 9 and 12 months after the beginning of therapy (secondary and tertiary endpoint).** According to the SOPHO-NET [36] and the study by Knekt and colleagues [4], we expect both CBT and ST to show stable effects on primary and secondary outcomes during the follow-up period.

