##### Therapy (T1 to T5)

We will assess study outcomes before the start of therapy, after the 8th, 15th and 20th hour of therapy, as well as after therapy has ended. At each time of assessment, patients will participate in an online survey (UNIPARK) including study outcomes (Table 1). The assessment will be conducted at the IMP. Baseline data (T1) will be scheduled no more than 5 days before the first therapy session. Therapy process (T2 to T4) will be assessed no more than 5 days after the 8th, 15th and 20th hour of therapy. The primary endpoint (T5) will be defined by a joint patient-therapist decision to end therapy or by the end of 26 hours of therapy. All outcome variables will be assessed anew, along with in- and outpatient health care service data. A post-SCID and social network interview will also be conducted. Like the pre-SCID, the post-SCID interviews will be rated by independent raters considering primary and secondary diagnoses.

**Table 1 Tab1:** Assessment measures and application plan

Purpose	Perspective	Domain	Instrument	Screening	Baseline	8th, 15th, 20th hour of therapy	End of therapy, no later than 26th hour of therapy	9 and 12 months after beginning of therapy
					T1	T2 to T4	T5	T6 and T7
Screening	Pat	Social anxiety	LSAS-SR	X				
	Diag	Mental disorder SAD	SCID: SAD	X				
Outcome	Diag	Mental disorders	SCID I, II	X			X	
	Pat	Social anxiety	LSAS-SR	X	X	X	X	X
	Pat	Social anxiety	SIAS	X	X	X	X	X
	Pat	Social anxiety	SPS	X	X	X	X	X
	Diag	Global functioning	GAF	X	X		X	
	Pat	Depression	BDI-II	X	X	X	X	X
	Pat, Ref	General symptom severity	BSI	X	X	X	X	X
	Pat, Ref	Experience of social systems	EXIS	X	X	X	X	X
	Pat, Ref	Evaluation of social systems	EVOS	X	X	X	X	X
	Pat, Ref	Dyadic adjustment	DAS-12	X	X	X	X	X
	Pat	Interpersonal problems	IIP-32	X	X	X	X	X
	Pat, Ref	Symptom adjustment	ASS	X	X	X	X	X
	Ref	Burden	BAS		X	X	X	X
Process	Pat, T	Therapeutic alliance	SACiP			X	X	X
	Pat, T	Therapeutic relationship	SRS			X	X	X
	Pat	Therapy motivation	URICA			X	X	X
	Pat, T	Credibility	OAT		X			
Therapists	T	Common therapist factors	DPCCQ		X	X	X	X
Quality	R	Adherence and competence	STAS, CTAS-SP		X	X	X	X
Additional service	Pat	Service receipt	CSSRI-EU				X	X

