### Statistical analyses

All statistics will be descriptive and explorative using the SPSS statistical package (version 19.0; IBM, Frankfurt, Germany). In addition to descriptive measures such as mean, standard deviation, median, interquartile range and confidence intervals, comparisons of primary endpoints between the two groups will be performed using t-test, Mann–Whitney U test and chi-square test, as appropriate. Missing values on less than 20 % of items for each scale of all outcome measures will be replaced with the conditional mean values for the CBT or ST group.

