#### Intention-to-treat and per-protocol analyses

The main analyses of all outcomes will be conducted on the intention-to-treat sample, comparing both treatment groups with 32 participants originally allocated after randomization [93]. This calculation will be regardless of whether the patients are detected to violate inclusion criteria, whether they complete therapy or not, or whether they are withdrawn from the study sample due to protocol deviations (e.g. changed use of medication, concurrent psychotherapy during the study period [94]). This will be followed by per-protocol analysis for the primary outcome measures (LSAS, SIAS, SPS) with only patients who fulfill all inclusion criteria, complete the intervention and do not deviate from the protocol.

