#### Mixed-design ANOVA

We will perform mixed-design ANOVA to identify differences between treatment conditions [95]. Factors will be group (CBT or ST) and time (baseline, 8th, 15th, 20th therapy hour, end of therapy, respectively 26th therapy hour, 9 and 12 months after the beginning of therapy). Contrasts A will compare baseline with end of therapy. Contrasts B will indicate change between end of therapy, respectively 26th therapy hour, and 9 months after the beginning of therapy. Contrasts C will indicate change between end of therapy and 12 months after the beginning of therapy. We will control for differences in the length of treatment.

Time X Group interaction effect sizes will be assessed with partial eta-squared (η^2^) for the mixed-design ANOVA. Classification of effect sizes will be: η^2^ ≥ 0.01, small effect; η^2^ ≥ 0.06, medium effect; and η^2^ ≥ 0.14, large effect. Subsequently, for significant Time X Group interactions, simple effect analyses within and between groups will be performed [96]. Between-group effect sizes will be assessed with η^2^ and Cohen’s *d*. Classification of Cohen’s *d* will be: *d* ≥0.20, small effect; *d* ≥0.50, medium effect; and *d* ≥0.80, large effect [34]. In accordance with Coe [97], we will interpret Cohen’s *d* in terms of percentiles. Within-group effect sizes will be assessed with η^2^.

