## Discussion

To the best of our knowledge, this will be the first prospective, open, interventive, balanced, bi-centric, explanatory pilot RCT comparing CBT, thoroughly evaluated for social anxiety disorders, and ST, a well-researched treatment approach that needs more evaluation with socially anxious patients. For study purposes, it is a challenge to make these two different approaches comparable in terms of manualization, duration of treatment, number of sessions, qualifications of therapists, institutional procedures, and allegiances of therapists and researchers. There are many differences that we will need to bridge. CBT is paid for by health insurances; ST is not. CBT training is state-regulated; ST training is regulated by professional associations. CBT is practiced almost exclusively by psychologists; ST by psychologists, social workers and other mental health professionals. CBT tends to use more sessions with shorter between-session intervals, and it does not intend to include important caregivers in treatment like ST does.

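### The ANOVA behind the Time X Group effect size is adjusted for treatment length, a post-randomization variable, so it may not estimate the randomized effect needed to size the main trial

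*Protocol article*

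**What the plan says.** All references are to the protocol article.

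- **The adjustment.** After defining Contrasts A, B and C, the section Mixed-design ANOVA states "We will control for differences in the length of treatment". It does not say whether length means hours, sessions or weeks, which contrasts are meant, or what form the adjustment takes. Nothing marks it as a sensitivity analysis. The next paragraph begins "Time X Group interaction effect sizes will be assessed with partial eta-squared".
- **How length arises.** Under Therapy (T1 to T5), the primary endpoint is "defined by a joint patient-therapist decision to end therapy or by the end of 26 hours of therapy".
- **Length and arm.** The Discussion counts duration and number of sessions among the features that are hard to make comparable, and adds that "CBT tends to use more sessions with shorter between-session intervals".
- **Purpose.** Under Hypotheses, the main question is "what effect sizes of ST can be expected compared to CBT, to calculate how many patients will be needed".
- **Main analysis set.** "The main analyses of all outcomes will be conducted on the intention-to-treat sample", whether or not therapy was completed.
- **A second comparison.** The opening paragraph of Statistical analyses says "comparisons of primary endpoints between the two groups will be performed using t-test", Mann–Whitney U or chi-square as appropriate. No covariate is mentioned there.

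**The concern.** Randomization protects the comparison of outcomes between arms. It does not protect a comparison made at equal treatment length, because length is decided during therapy. A patient may stop early because of a good response or because therapy is not helping, and the two approaches may use their hours differently. Holding length fixed then has two effects. It removes whatever part of the arm difference runs through the amount of therapy, and it can compare patients of different prognosis across arms.

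In many pilots this would matter little. Here the between-arm effect size is the product: it is meant to set the size of the confirmatory trial. An effect size with an unintended meaning would carry straight into that calculation.

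**Working it through.** **1. The plan's own figures.** Design and sample size cites a main trial of 350 for a difference of 0.3 SD (80 % power, two-sided 5 %) and a pilot of 32.

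- Per arm: 2 × (1.960 + 0.842)² / 0.3² = 2 × 7.85 / 0.09 = 174.4, rounded up to 175; total 350.
- 32 / 350 = 9.1 %.
- One-sided 80 % confidence distance with 16 per arm: 0.842 × √(2/16) = 0.298 SD, just under 0.3.

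These reproduce. No stated figure is wrong.

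**2. What the covariate does.** Let d be the total randomized effect on improvement (CBT minus ST, within-arm SD 1). Let a be the CBT-minus-ST difference in mean length, in within-arm SDs, and r the within-arm correlation of length with improvement. With a common slope,

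adjusted effect = d − r × a.

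The shift is zero if r = 0 or a = 0. Its sign follows the sign of r × a. For the contrast over time, it applies when length is allowed to relate to change, that is, to interact with time.

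**3. Illustration.** The protocol gives neither a nor r; both are assumed. I set d = 0.30 only so that the result can be read against 350. Total N = 2 × (15.70 / effect², rounded up).

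| a | r | Adjusted effect | Shift | Implied N |
|---|---|---|---|---|
| any | 0 | 0.300 | 0 | 350 |
| 0 | any | 0.300 | 0 | 350 |
| 0.25 | −0.3 | 0.30 + 0.075 = 0.375 | +0.075 | 224 |
| 0.25 | +0.3 | 0.30 − 0.075 = 0.225 | −0.075 | 622 |
| 0.5 | −0.3 | 0.30 + 0.15 = 0.45 | +0.15 | 156 |
| 0.5 | +0.3 | 0.30 − 0.15 = 0.15 | −0.15 | 1396 |

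A large-sample simulation agreed with the formula (0.376, 0.227, 0.444 and 0.146 for the last four rows). With longer CBT (a > 0), a negative r fits early responders stopping early, and a positive r fits short, poor courses.

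**4. Length driven only by response.** Then a = r × d, so the adjusted effect is d × (1 − r²). For |r| = 0.3 this is 0.30 × 0.91 = 0.273 (N = 422). For |r| = 0.5 it is 0.30 × 0.75 = 0.225 (N = 622). The shift is 0.027 to 0.075 SD, always toward zero, and nil if d = 0.

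**The case against.** The case on the other side has several sound parts.

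- **An apparently unadjusted comparison is already planned.** The endpoint tests in the opening paragraph of Statistical analyses carry no covariate, and the text does not say that Cohen's d comes from the adjusted model. So it cannot be said that every arm comparison is adjusted. What remains is that partial eta-squared for Time X Group is tied to the ANOVA, and the protocol does not say which estimate will size the main trial.
- **The sentence may have a legitimate purpose.** It follows Contrasts B and C, which run from a variable end of therapy to fixed times after its beginning. Their intervals therefore depend on treatment length. This argues against simply deleting the adjustment. It does not justify applying it to the main contrast.
- **A reader might infer that the arms are stated to differ in length.** They are not. The Discussion describes a tendency, among differences the authors mean to bridge. The 26-hour cap limits differences in hours, and more sessions at shorter intervals need not take longer in weeks.
- **A reader might infer a contradiction with intention to treat.** That section fixes who is analysed, and a covariate leaves the sample unchanged. The problem is which effect is estimated.
- **Noise is larger than the illustrated bias.** With 16 per arm the standard error is about √(2/16) = 0.35 SD. This is true, but sampling error is visible in a confidence interval and this bias is not.

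**Conclusion.** The point holds in a limited form. As written, the adjustment puts a post-randomization variable into the model that supplies the Time X Group effect size. If length is related to outcome and either differs by arm or follows response, that effect size is not the total randomized effect of ST versus CBT. That length follows response is a plausible inference from the joint decision to end therapy; the protocol does not report it.

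The sign and size of the bias are unknown. The shift of about 0.08 to 0.15 SD rests wholly on the assumed a of 0.25 to 0.5 SD and r of ±0.3. A reader might go further and conclude that the covariate will move the effect by as much as 0.3 SD or more, or could by itself confirm or reverse H1. The protocol does not support this. It gives no value for a or r. The 0.3 SD is the supposition of the cited pilot-sample-size paper, not a target set for this trial. All analyses are declared descriptive and explorative, with confirmatory statements reserved for the main trial.

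**What to change.** 1. Estimate the between-arm effect size for Contrast A (baseline to end of therapy) without the length covariate, and name it as the estimate used to plan the main trial. This agrees with the apparently unadjusted endpoint tests already planned.
2. Report hours and weeks of therapy by arm as descriptive results.
3. Keep any length-adjusted analysis, including one for the unequal intervals in Contrasts B and C, as a labelled supplementary analysis that does not estimate the treatment effect. State how length is measured in it.

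This needs a change of wording only. It requires no further patients or data and leaves the sample of 32 as it is. The small downside is that the unequal follow-up intervals in Contrasts B and C are then addressed only in the supplementary analysis.

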## Methods

### Design and sample size

This pilot study is a prospective, open, interventive, balanced, bi-centric^1^, explorative RCT. The aim is to compare CBT and ST for social anxiety disorders. According to Cocks and Torgerson [47] for two-arm pilot studies of this kind, we will recruit 32 patients; 16 patients per CBT and ST, respectively (Fig. 1). Cocks and Torgerson used a confidence interval (CI) approach to calculate pilot sample sizes for continuous outcome measures. They supposed 0.3 of a standard deviation between two groups to be worthwhile, and stated that such a study would require 350 participants (assuming 80 % power and a two-sided alpha of 5 %). For pilot studies of which the primary goal is testing of the recruitment rate, they found 32 patients (approximately 9 % of the main sample size) to be required to produce a one-sided 80 % confidence limit. Cocks and Torgerson concluded that a pilot trial with that sample size, showed an estimate larger than zero and demonstrated feasibility to recruit and retain the patients, and so forth, should move forward with the main study.

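### Uncorrected partial eta-squared for Time X Group averages 0.032 with identical therapies at 16 per arm, three times the cut for a small effect; report a bias-corrected measure and plan the main trial from d

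*Protocol article*

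**What the plan says.** The Hypotheses section makes effect size the pilot's main question: "what effect sizes of ST can be expected compared to CBT, to calculate how many patients will be needed" in a later trial. The Mixed-design ANOVA section then fixes the measure: "Time X Group interaction effect sizes will be assessed with partial eta-squared", with "η^2^ ≥ 0.01, small effect" as the lowest class, 0.06 as medium and 0.14 as large. The factors are group and "time (baseline, 8th, 15th, 20th therapy hour, end of therapy, respectively 26th therapy hour, 9 and 12 months after the beginning of therapy", that is, seven occasions. "Contrasts A will compare baseline with end of therapy", which is the comparison that bears on the primary endpoint.

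The same section runs simple-effect analyses only after a significant interaction. It then introduces between-group eta-squared and Cohen's d, with d cuts at 0.20, 0.50 and 0.80. It does not say whether d is reported when the interaction is not significant, or which measure will be used to size the later trial.

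The sample is "16 patients per CBT and ST, respectively", and the main analysis is by intention to treat, "comparing both treatment groups with 32 participants originally allocated after randomization". The size was taken from a methodological source, described under Design and sample size: "They supposed 0.3 of a standard deviation between two groups to be worthwhile".

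**The concern.** Sample partial eta-squared is a ratio of sums of squares. It cannot be negative, so chance differences between the arms always push it above zero and never below. In a large trial the bias is negligible. With 32 patients it may be larger than the lowest class boundary, and that boundary would then say little about whether the therapies differ.

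The stake is the pilot's stated product. An effect described as small or medium is what readers and planners will remember, and an upward-biased value carried into a sample-size calculation would overstate the effect to be detected.

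**Working it through.** **Inputs.** From the article: 32 patients, 16 per arm; seven occasions; cuts 0.01, 0.06 and 0.14 for eta-squared and 0.20, 0.50 and 0.80 for d; a worthwhile difference of 0.3 SD; 80 % power and two-sided alpha of 5 %. Assumed, because the article does not give them: complete data, the within-patient correlation pattern, and an SD of change of 1 (a baseline to end-of-therapy correlation of 0.5, with unit SD at both times).

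**The article's own figures.** Per arm, 2 × (2.802/0.3)² = 174.4, rounded up to 175, so 350 in total. Pilot size from a one-sided 80 % limit: 4 × (0.8416/0.3)² = 31.5, rounded up to 32. Both reproduce, and both are on the SD scale, not the eta-squared scale.

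**Mean with no true difference.** Under sphericity, partial eta-squared follows a Beta(df1/2, df2/2) distribution with mean df1/(df1 + df2).

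- Seven-occasion interaction: df1 = 6, df2 = 6 × 30 = 180, mean 6/186 = 0.032.
- Contrast A: df1 = 1, df2 = 30, mean 1/31 = 0.032.

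Both are a little over three times the 0.01 cut.

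**How often identical therapies receive a label.** P(eta² ≥ t) = P(F ≥ [t/(1 − t)] × df2/df1). Since df2/df1 = 30 in both cases, the thresholds are F = 0.303, 1.915 and 4.884.

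| No true difference | at least small | at least medium | large |
|---|---|---|---|
| Interaction, F(6,180) | 93.5 % | 8.1 % | 0.01 % |
| Contrast A, F(1,30) | 58.6 % | 17.7 % | 3.5 % |
| Cohen's d, 16 per arm | 57.6 % | 16.8 % | 3.1 % |

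**Sensitivity of the interaction row.** In simulations of 100,000 null trials per pattern, the rate of at least small was 91.4 % under first-order serial correlation of 0.5, 89.1 % at 0.7, 87.8 % at 0.8, 85.7 % at 0.9 and 84.7 % at 0.95. Random-slope patterns gave 90 to 93 %. The mean stayed at 0.032 throughout. Adjusting for length of treatment (df2 = 174) gives a mean of 6/180 = 0.033 and 94.0 %. If only 24 patients were analysed, the mean would be 1/23 = 0.043 and the rates 97 % (interaction) and 64 % (contrast).

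**With a real difference.** At a true 0.3 SD on Contrast A, with SD of change 1, true eta² = 0.3²/(0.3² + 4) = 0.09/4.09 = 0.022. The simulated sample mean is 0.053, about 2.4 times the truth. Epsilon-squared, 1 − (1 − eta²)(df1 + df2)/df2, averages 0.021.

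**How often d would follow if gated.** With the same assumptions the noncentrality is 0.3² × 8 = 0.72, and the F(1,30) test is significant in about 13 % of pilots. Significance needs an observed d of about 2.042 × √(1/8) = 0.72.

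**What correction achieves.** With no difference, epsilon-squared averages zero and reaches 0.01 in 25 % (interaction) or 26 % (contrast) of trials.

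**The case against.** Several objections stand in whole or in part.

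- On Contrast A the mislabelling is not specific to eta-squared. With one degree of freedom, the cuts 0.01, 0.06 and 0.14 correspond to population |d| of 0.20, 0.51 and 0.81, from d = 2√[eta²/(1 − eta²)], and the table shows nearly equal rates. There the cause is the small sample. Only the interaction result is peculiar to eta-squared.
- The labels decide nothing. Follow-up analyses depend on significance, and the article calls all its analyses descriptive and explorative.
- Means, SDs, confidence intervals and d are all named in the article, so a signed SD-scale estimate can be obtained.
- Bias correction removes the average error, not the noise: a quarter of null trials still pass 0.01.

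A reader might also infer three stronger things that the article does not support. One is that the measure can never show the absence of an effect; in fact about 6 to 15 % of null trials fall below 0.01 on the interaction and 41 % on Contrast A. Another is that direction would be lost; group means and d show it. The third is that the main trial will be undersized by a definite number of patients. No section says that eta-squared will enter that calculation. Converting the null mean into a sample size and setting it against 350 would compare a no-difference case with a true 0.3 SD.

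What remains is that the stated estimator is biased upward by more than its lowest cut, and that the article does not guarantee that the better estimate is reported or used for planning.

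**Conclusion.** The point holds as a recommended change to the choice of effect measure, not as an error that invalidates the pilot. The null mean of 0.032 is exact for 16 per arm with complete data under sphericity, and simulation shows it unchanged under the other correlation patterns tried. The lowest label therefore barely separates an effect from none on the seven-occasion interaction: 85 to 94 % of null trials receive it, a range that rests on the assumed correlations. On Contrast A the figure is 59 %, chiefly a consequence of 32 patients. The overstatement at a true 0.3 SD (0.053 against 0.022) rests on the assumed SD of change of 1. It would harm planning only if eta-squared were used for planning, which the article neither states nor excludes. On the reading that d follows only a significant interaction, eta-squared would usually be the only between-arm effect size reported.

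**What to change.** In the Mixed-design ANOVA section:

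1. Report the Time X Group effect and Contrasts A to C with epsilon- or omega-squared and a confidence interval, in place of uncorrected partial eta-squared.
2. Do not attach the small, medium and large labels to pilot point estimates, whether of eta-squared or of d. Removing them for eta-squared alone would leave the same problem on the contrasts.
3. State that planning of the main trial uses the signed, small-sample-corrected end-of-therapy d with its confidence interval, and that d is reported whether or not the interaction is significant.

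The cost is a few sentences and a few lines of post-processing of the ANOVA output. No data collection changes. The downside is presentational: reported effects will look smaller, epsilon- or omega-squared can come out negative, and the intervals will be wide, which reflects what 32 patients can show.

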Considering ST, we found only three RCTs for anxiety disorders [4–6], and only two of them investigated social anxiety disorders. One RCT (*n* = 120, Poland) compared 10 weeks of brief strategic therapy (BST) with MST. The outcome relied on the Interpersonal Sensitivity, Anxiety and Global Severity Index of the Symptom Checklist-90-R (SCL-90-R) [39, 40]. This trial demonstrated BST superiority for patients with social anxiety disorders only (response: 50 % BST, 20 % MST) but no significance of any treatment for patients with comorbid personality disorders (response: 7 % BST and MST) [6]. The second RCT (*n* = 83, Germany) compared a combined resource-oriented cognitive-behavioral therapy (ROCBT) with CBT. The main outcomes were the Social Interaction Anxiety Scale (SIAS) and Social Phobia Scale (SPS). SIAS and SPS are original German scales and were developed by the leading German CBT researcher for social anxiety disorders [41–43]. This trial demonstrated ROCBT superiority (Cohen’s *d* = 1.29, for both SIAS and SPS) compared to CBT (*d* = 0.86, for SIAS; *d* = 0.97, for SPS). Therapy effects were stable over the 2- and 10-year follow-up in both treatment conditions [5]. The third RCT (*n* = 326, Finland) compared long- and short-term PD with solution-focused ST. This study included patients with both mood and anxiety disorders. Results indicated a statistically significant reduction of symptoms on all outcomes in all three treatment groups during the 3-year study period, including the SCL-90-R anxiety subscale and the Hamilton Anxiety Rating Scale (HAM-A). Both instruments measure anxiety but not social anxiety [44]. The reduction was faster in short-term psychotherapies, including the solution-focused ST during the first year of follow-up. However, the reduction continued during the 3-year follow-up only for the long-term PD [4].

Consequently, none of the above described ST RCTs used the LSAS, though it is most often used for the assessment of social anxiety disorders [45]. The SOPHO-NET used the LSAS as the main outcome for that reason [35]. Willutzki and colleagues decided to use the original German SIAS and SPS, which highly correlate with the LSAS [5]. We therefore miss information regarding the efficacy of multi-person ST on established social anxiety assessments, such as the LSAS, SIAS and SPS. Additionally, we also miss information regarding the efficacy of multi-person ST when compared to a well-established comparator, the CBT.

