### Innovative aspects

This trial will be the first pilot study that directly compares CBT and ST, integrating a broad range of systemic methods, for social anxiety disorders. Former studies used either MST [6], an incremental design [5], PD, or did not focus on social anxiety disorders but mood and anxiety disorders in general [4]. The times of measurement and the instruments we will use are aligned with these three studies and the SOPHO-NET [48], allowing for direct comparisons of results.

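### Within-group change is measured by partial η² alone, and the only η² cut-offs given fit independent groups, so 'large' begins well below the plan's own d of 0.80

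*Protocol article*

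**What the plan says.** All of this is in the Mixed-design ANOVA section unless stated otherwise.

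- Time-by-group "interaction effect sizes will be assessed with partial eta-squared".
- "Classification of effect sizes will be" small from 0.01, medium from 0.06 and large from 0.14 on η². No other η² scale appears in the article.
- After a significant time-by-group interaction, "simple effect analyses within and between groups will be performed".
- "Between-group effect sizes will be assessed with" both η² and Cohen's d. The d cut-offs are 0.20, 0.50 and "≥0.80, large effect".
- "Within-group effect sizes will be assessed with" η². No d is named for change within an arm.

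Elsewhere, the Efficacy section gives one Cohen's d per arm for one earlier trial. It says "This trial demonstrated ROCBT superiority" with d = 1.29 on both SIAS and SPS, against CBT values of 0.86 (SIAS) and 0.97 (SPS). Innovative aspects says that measurement times and instruments are aligned with earlier studies, "allowing for direct comparisons of results". The opening of Statistical analyses plans means, SDs and confidence intervals.

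**The concern.** The section sets two effect-size scales side by side. They agree when two independent groups are compared. They do not agree for change within one arm, because partial η² is then driven by the variability of the change score rather than of the score itself. The more strongly the pre and post scores correlate, the larger η² becomes for the same improvement in score units. A reader who applies the only η² scale on offer would call a change 'large' at a size that the d scale calls small or medium.

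Two things are at stake. The first part of H1 expects both therapies to reduce social anxiety, and the within-group effect size is where the extent of that reduction would be graded. The article also wants its results read beside earlier trials, and a within-group η² cannot be read beside a d unless r and the error term are known.

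**Working it through.** **Inputs from the protocol article.** η² cut-offs 0.01, 0.06, 0.14; d cut-offs 0.20, 0.50, 0.80; η² introduced as partial; 16 patients per arm (Design and sample size); a baseline-to-end-of-therapy contrast with two time points; per-arm d values 0.86, 0.97 and 1.29 (Efficacy).

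**Assumptions.** The pre-post correlation r is not given, so r = 0.3 to 0.8 is used. Pre and post SDs are taken as equal. The error term is not given, so both candidates are shown.

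**Step 1: reproduce the plan's cut-offs.** For two equal independent groups, η² = d²/(d² + 4).

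- d = 0.20: 0.04/4.04 = 0.0099
- d = 0.50: 0.25/4.25 = 0.0588
- d = 0.80: 0.64/4.64 = 0.1379

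Rounded, these are 0.01, 0.06 and 0.14. The two scales are therefore the same scale for an independent-group comparison.

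**Step 2: pre-post change in one arm.** Let dz be the mean change divided by the SD of change. Partial η² = n·dz²/(n·dz² + df), so dz = √[η²·df/((1 − η²)·n)]. On the raw-score SD, d = dz·√[2(1 − r)].

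At η² = 0.14 and n = 16:

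- arm's own error, df = 15: dz = √(0.14 × 15/(0.86 × 16)) = 0.39
- error pooled over both arms, df = 30: dz = √(0.14 × 30/(0.86 × 16)) = 0.55

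Raw-SD d that just reaches 'large', with its share of 0.80:

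| r (assumed) | own error | pooled error |
|---|---|---|
| 0.3 | 0.46 (58 %) | 0.65 (82 %) |
| 0.5 | 0.39 (49 %) | 0.55 (69 %) |
| 0.7 | 0.30 (38 %) | 0.43 (53 %) |
| 0.8 | 0.25 (31 %) | 0.35 (44 %) |

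Every entry is below 0.80, and the size of the gap depends on r and the error term.

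**Step 3: the same point in reverse.** A within-arm d of 0.80 corresponds to partial η² = 0.33, 0.41 and 0.53 at r = 0.3, 0.5 and 0.7 (own error), not 0.14. For example, at r = 0.5: 16 × 0.64/(16 × 0.64 + 15) = 10.24/25.24 = 0.41.

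**Step 4: comparability with the quoted d values.** Read as within-arm change (the article does not say how they were standardised), own error, n = 16:

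| d | r = 0.3 | r = 0.5 | r = 0.7 |
|---|---|---|---|
| 0.86 | 0.36 | 0.44 | 0.57 |
| 0.97 | 0.42 | 0.50 | 0.63 |
| 1.29 | 0.56 | 0.64 | 0.75 |

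The smaller effect can have the larger η²: 0.86 at r = 0.5 gives 0.44, while 0.97 at r = 0.3 gives 0.42.

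**Step 5: sensitivity to the kind of η².** With classical (non-partial) η² over two time points, η² = d²/(d² + 4(n − 1)/n). The 0.14 cut-off then falls at d = √(0.14 × 3.75/0.86) = 0.78, and the distortion all but disappears. The result therefore rests on η² being partial, as the section introduces it.

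**The case against.** The case on the other side is substantial.

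- **No rule expressly grades within-group η².** The cut-offs follow the interaction sentence, and the final sentence attaches no labels. This stands. Applying them is the natural reading because no other η² scale is given, but it is an inference.
- **The gate.** Within-group effects are examined only after a significant interaction. This stands. A reader might infer that a weak ST effect would routinely be called 'large': with a true d of 0.40 and the arm's own error, that happens in 53 % (r = 0.5) or 70 % (r = 0.7) of trials if the gate is ignored. Suppose CBT has d = 0.86, and take the interaction as the baseline-to-end contrast at a two-sided 5 % level. The interaction is then significant in about 24 % or 37 % of trials, and ST is both tested and labelled 'large' in about 5 % or 17 %. These figures move with the assumed CBT effect, so no single frequency follows from the plan.
- **Comparison is still possible.** This stands. Means and SDs are planned, so a d can be computed. The article bases comparability on measurement times and instruments, not on an effect metric, and it gives d values for only one of the cited trials. A reader might infer that comparison with earlier trials is lost; the documents do not support that.
- **Little depends on it.** This stands in part. The study is exploratory, and the between-group comparison that informs the main trial already uses Cohen's d. It does not make η² a suitable sole measure of within-group change.

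**Conclusion.** The point holds in a limited form. The plan's η² cut-offs are those for independent groups, and the sole measure that it names for within-group change is partial η², which depends on an unstated correlation and error term. If the cut-offs are applied there, 'large' starts at a raw-SD d between 0.25 and 0.65 rather than 0.80, for r from 0.3 to 0.8 and either error term with 16 per arm.

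A reader might infer that 'large' always starts at half the plan's own d or less. That needs r of at least about 0.48 with the arm's own error, or about 0.74 with pooled error, and the article fixes neither. What can be said is that the threshold lies below 0.80 in every partial-η² case examined.

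The consequence is confined to how within-group change is described and compared. The between-group d, and hence the planning of the main trial, does not carry this scale problem.

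**What to change.** Replace the last sentence of the Mixed-design ANOVA section with:

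> Within-group change will be reported as mean change from T1 divided by the T1 SD (pooled over arms), with a 95 % CI, together with the raw mean change, its SD and the pre-post correlation. The η² cut-offs are not applied to within-group change.

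Naming the standardiser fixes the scale. Reporting the SD of change and the correlation lets others convert to another metric and supplies inputs for planning the main trial. The cost is a change of wording in the analysis plan; data, assessments and software stay the same.
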